### Cost-Effectiveness Analysis

Cost-effectiveness analysis will consist of a simulation with a Markov model to compare two strategies applicable to CRC prevention in a cohort of 5000 FDRs of patients with CRC: 1) Annual FIT and colonoscopy if the test result is positive; and 2) direct colonoscopy from the start of the screening period.

Transition probabilities between the different states the subjects may undergo will be derived from the literature and results arising from this study. Cost estimates of each event where either screening strategy is performed will be based on those published in the Official Gazette of the Canary Islands. An annual discount rate of 3% will be considered.

The following criteria will be established for model development: 1) The target population (FDRs) will be that defined in the inclusion criteria of this study; 2) In FDRs who are assigned annual FIT, the following transition states will be considered: FIT in the first, second, and third years, colonoscopy after positive FIT results, non-advanced neoplasia diagnosis, advanced neoplasia diagnosis, invasive CRC diagnosis and monitoring; 3) In FDRs who are assigned direct colonoscopy, the transition states will be: colonoscopy in the first year, colonoscopy in the second year if advanced neoplasia of >20 mm is detected, non-advanced neoplasia diagnosis, advanced neoplasia diagnosis, invasive CRC diagnosis and monitoring; 4) Since FIT will be conducted annually, the length of each Markov cycle is set to one year, with a half-cycle correction; 5) A time limit of three years from the perspective of the National Health System will be considered, where only direct healthcare costs are included; 6) Estimated health costs will be: FIT kit, automated analysis, colonoscopy, polypectomy, cost per day of hospital stay when required (polypectomy bleeding, perforation, CRC surgery), cost per surgical procedure (laparoscopy or openlaparotomy) and colectomy; 7) It will be assumed that all lesions detected at colonoscopy are resected and colonoscopies are carried out in full.

The described model will be used to develop a cost analysis including sensitivity analysis of all variables in the model to test its robustness and identify situations that could change the decision strategy. Variables to be considered in the sensitivity analysis are as follows: adherence to the program, adherence to the various rounds of FIT screening, rate of complications, sensitivity and specificity of FIT and discount rate. Cost-effectiveness analysis will be carried out, defining effectiveness as the number of patients in whom a significant colonic lesion (advanced neoplasia) was detected. Calculation of the incremental cost-effectiveness ratio (ICER) will be performed using the following formula:

ICER = Cost b - Cost a

*Effectiveness* b - *Effectiveness* a

where ‘*b*’ is the compared option (annual FIT) and ‘*a*’ is the reference option (one time colonoscopy). ICER is defined as the increase in the average cost of obtaining an additional unit of effectiveness if option "*b*" is used instead of option "a".

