### Study variables and procedures.

***Colonoscopy***: colonoscopies will be performed by experienced endoscopists who have performed > 200 scans and > 50 polypectomies in the previous year. Sedation and colon cleansing will be performed as previously described (Parra et al. World J Gastroenterol 2006). The Boston classification will be used as a scale for bowel cleansing and it will be considered to be adequate when the score is ≥ 2 points in each segment (Lai EJ, et al Gastrointest Endosc 2009). Each colon segment consists of "ascending colon and cecum", "transverse colon" and "descending colon, sigmoid and rectum ', amounting to a minimum of 6 points in the Boston classification (Lai EJ, et al Gastrointest Endosc 2009). Colonoscopy will be considered complete when cleansing is adequate and the cecum is reached. Otherwise the colonoscopy will be considered incomplete and shall be repeated.

***Polyp features:*** Polyp location will be recorded by segmentation. Polyp size and morphology will be recorded using the Paris classification (Gastrointest Endosc 2003:58, Suppl S3-S43). Whether the polyp was removed whole or by fragments will also be recorded. Lesions will be classified as distal or proximal to the splenic flexure. Adenomas ≥ 10 mm in size, with tubulovillous architecture, with high- grade dysplasia or *in situ* adenocarcinoma -pTis- will be considered to be advanced adenomas. Invasive CRC occurs when neoplastic cells cross the *muscularis mucosae*. Advanced neoplasia is the name given to advanced adenomas or invasive CRC. Serrated polyps will be classified according to the World Health Organization (WHO) classification as hyperplastic polyps, sessile serrated adenomas with or without dysplasia and traditional serrated adenomas. In patients with advanced adenoma >20 mm or with advanced adenoma resected in multiple fragments, a surveillance colonoscopy will be performed at 6-12 months after the previous colonoscopy.

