### Year 3 (Februry 2018 to February 2019)

- Completion of the 3^rd^ screening round in the FIT group.
- Performance of colonoscopies of randomized patients (1^st^ to 4^th^ quarter), colonoscopies of patients with positive FIT results, repetition of incomplete colonoscopies and repetition of colonoscopies in which high-risk polyps were found or where piecemeal resection of these polyps was performed.
- Cost-effectiveness analysis (3^rd^ and 4^th^ quarter).

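### The Markov model lists a second-year surveillance colonoscopy for one strategy only, on a narrower trigger than the trial's own rule, so incremental cost may be biased

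*Supplement*

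**What the plan says.** The Cost-Effectiveness Analysis section lists the states of each strategy.

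- **FIT:** "FIT in the first, second, and third years, colonoscopy after positive FIT results, non-advanced neoplasia diagnosis, advanced neoplasia diagnosis, invasive CRC diagnosis and monitoring".
- **Direct colonoscopy:** a first-year colonoscopy, then "colonoscopy in the second year if advanced neoplasia of >20 mm is detected", then the same three diagnosis states and the same closing monitoring state. Monitoring is not defined for either strategy.

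The horizon is short: "A time limit of three years from the perspective of the National Health System will be considered", in one-year cycles and with direct healthcare costs only.

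The rule for trial participants is in Study variables and procedures, under polyp features: "In patients with advanced adenoma >20 mm or with advanced adenoma resected in multiple fragments, a surveillance colonoscopy will be performed at 6-12 months" of the previous examination. It is not restricted by arm. The workplan for Years 2 and 3 likewise plans "repetition of colonoscopies in which high-risk polyps were found or where piecemeal resection of these polyps was performed", in the same list as colonoscopies of randomized participants and colonoscopies after a positive FIT.

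Amendments 1 to 3 do not change the model.

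**The concern.** Cost-effectiveness is a stated secondary outcome. Followed as written, the model charges by name, to one strategy only, a procedure that the protocol prescribes for qualifying lesions in both. It also charges it on a narrower trigger, because removal in several pieces is left out.

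The error would fall on the numerator of the ICER. Effectiveness is the number of patients with advanced neoplasia detected, so a surveillance examination adds cost and essentially no effect. The plan's hypothesis is similar diagnostic efficiency, so the denominator may be small, and a modest error in cost could then move the ratio noticeably.

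The planned sensitivity analyses would not catch this. The named variables are adherence, complications, FIT accuracy and the discount rate. The Monte Carlo analysis draws transition probabilities between the states that the model contains, and an absent state has none to draw.

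**Working it through.** **No stated figure to reproduce.** The documents give no unit costs, surveillance rate, lesion-size distribution or ICER. The check is a comparison of the sections, then an illustrative count.

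**1. The sections side by side**

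| | Trial rule | Model, direct colonoscopy | Model, FIT |
|---|---|---|---|
| Surveillance colonoscopy named | yes, either arm | yes | no |
| Lesion >20 mm is a trigger | yes | yes | – |
| Piecemeal removal is a trigger | yes | no | – |
| Lesion class | advanced adenoma | advanced neoplasia | – |
| Monitoring state | – | listed, undefined | listed, undefined |

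**2. Can monitoring close the gap?** There are three readings.

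- It holds no surveillance in either arm: FIT lacks a procedure that the comparator has.
- It holds surveillance in both arms: the comparator has it there and again as a named state, so it may be counted twice.
- It holds surveillance for FIT only: the arms then match for lesions >20 mm, but nothing in the text says that one word has two meanings.

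**3. Illustrative count under the first reading, with the cohort of 5,000 applied to each strategy**

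Inputs from the documents:
- Uptake is 34.1% for colonoscopy and 35.9% for FIT (Amendment 1). Screened: 5,000 × 0.341 = 1,705 and 5,000 × 0.359 = 1,795.
- s, the share of qualifying lesions found by the FIT strategy, is 0.29 to 0.80. This is borrowed from the pilot-study sensitivity range in the Background and may not carry over to lesions of this size.

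Assumptions not in the documents:
- q, the prevalence of advanced lesions >20 mm among those screened: 0.5% to 3%.
- r, the number of piecemeal-resected advanced adenomas of 20 mm or less per lesion >20 mm: 0 to 1.

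Surveillance colonoscopies omitted:
- FIT = 1,795 × s × q × (1 + r)
- Colonoscopy = 1,705 × q × r
- Net = FIT − colonoscopy. A positive net means that FIT cost is understated relative to colonoscopy.

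At q = 1%:

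| s | r | FIT omits | Colonoscopy omits | Net |
|---|---|---|---|---|
| 0.29 | 0 | 5.2 | 0 | +5.2 |
| 0.80 | 0 | 14.4 | 0 | +14.4 |
| 0.29 | 1 | 10.4 | 17.1 | −6.6 |
| 0.80 | 1 | 28.7 | 17.1 | +11.7 |

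Extremes over the whole grid, both at q = 3%:
- s = 0.29, r = 1: 31.2 − 51.2 = −19.9
- s = 0.80, r = 0: 43.1 − 0 = +43.1

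Against the 1,705 primary colonoscopies these are −20/1,705 = −1.2% and 43/1,705 = +2.5%.

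**4. Where the sign changes.** Setting net = 0 gives r = 0.359s / (0.341 − 0.359s).
- s = 0.29: 0.1041 / 0.2369 = 0.44
- s = 0.80: 0.2872 / 0.0538 = 5.3
- s above 0.341/0.359 = 0.95: the sign never changes.

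The plan's similar-detection hypothesis corresponds to s near 1. At s = 1 and q = 1% the net is 17.95 − 0 = +18 for r = 0, and 35.9 − 17.05 = +19 for r = 1. At q = 3% these become +54 and +57.

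**5. Horizon.** Surveillance 6 to 12 months after a third-round FIT detection falls partly or wholly beyond year three. The FIT omissions above are therefore upper values for the given q, r and s.

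**The case against.** A reader might infer that FIT cost is understated and that the comparison is biased towards FIT in a known direction. The documents do not support that, for three reasons.

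- Monitoring is undefined and could carry surveillance. A short list of states need not name events in parallel, and colonoscopy is a generic cost item. The separate second-year state in the comparator makes this reading less natural, but the text does not exclude it. Even so, the section would need a definition.
- The narrow trigger works the other way in the colonoscopy arm, where leaving out piecemeal removals lowers cost. With low FIT detection the net can reverse. This stands, although one omission partly cancelling another is no reason to keep both.
- The three-year horizon removes part of the surveillance that FIT would generate. This also stands.

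A reader might also want to express the omission as a share of FIT work-up colonoscopies. The documents give no FIT positivity rate in this population, and careless pairings mislead. For example, 15% of screenees with advanced neoplasia detected and 15% FIT positivity would make every positive test a true positive.

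Finally, the point concerns one state in the model for a secondary outcome. It does not touch uptake or detection rates, and without unit costs no effect on the ICER can be shown.

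**Conclusion.** The asymmetry and the mismatch of triggers are plain on the text. The model names surveillance for one strategy only and leaves out a trigger that the protocol applies in both arms.

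The consequence is a possible bias in incremental cost. It is likely to favour FIT if the two strategies find a similar share of qualifying lesions, as the plan hypothesises, but it could go the other way if FIT finds few of them and piecemeal removals of smaller lesions are common. On the assumed q and r, with s from 0.29 to 0.80, the net runs from about −20 to +43 colonoscopies per 5,000 relatives, or about −1% to +2.5% of the comparator's primary colonoscopies. It is larger, up to +57, if FIT detection is complete and q is 3%. These figures show a plausible scale and are not estimates. The effect is probably modest, but it lies in the structure of the model, so the planned sensitivity analyses would not reveal it.

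**What to change.** - Reconcile the Cost-Effectiveness Analysis section with Study variables and procedures on a single surveillance trigger, including the lesion class. Which trigger applies is for the trial's clinical leads; the model should then follow it in both strategies.
- Give both strategies the same surveillance-colonoscopy state, entered in the cycle after any colonoscopy that meets the trigger and counted only within the three-year horizon.
- Define monitoring, so that surveillance is neither left out nor counted twice.
- Feed the state with the surveillance proportions observed in each arm. Follow-up and Amendment 2 already provide for identifying post-polypectomy surveillance through the medical records.
- Add the surveillance proportion to the named sensitivity variables and to the Monte Carlo inputs. Events will be few: at an assumed q of 1%, the 147 + 158 = 305 participants screened at the interim analysis would yield about three lesions >20 mm even if all were found. The input distribution should reflect that.

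The cost is one additional model state and a few sentences in the cost-effectiveness and sensitivity-analysis text. No new data collection is needed.

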Despite being the most widely used screening method in the population at familial risk, colonoscopy has numerous drawbacks. Firstly, between 20-26% of adenomas of any size and up to 6-12% of advanced lesions may be missed. Secondly, it is an expensive procedure that requires intravenous sedation and staff training. Thirdly, it is an invasive technique with risks of serious complications, although these are infrequent. Endoscopic polypectomy has a global rate of post-polypectomy bleeding or intestinal perforation of 0.26% and 0.04% of procedures, respectively [7]. However, risk of complications increases significantly if the polyp is located in the cecum or if the polyp is >20 mm in diameter [8]. Furthermore, beneficial effect of colonoscopy to reduce the incidence and mortality rates of CRC is significantly lower in tumors located in the right colon than in those located in the left colon [9]. Finally, its efficacy as a screening test in FDRs of patients with CRC is limited by poor adherence. Population studies conducted in Spain and Australia have found that only 38% and 20% of FDRs, respectively, receive a screening colonoscopy following the recommended timelines given by clinical practice guidelines [10,11].

Several studies have shown that screening by annual or biennial fecal occult blood test (FOBT) reduces CRC incidence and mortality in the average risk population, which consists of asymptomatic persons

≥50 years old with no family history of the disease [12]. In addition, a Spanish multicentre study in this same population showed that immunochemical fecal occult blood test (FIT) was better accepted than colonoscopy and showed a similar CRC detection efficacy [13]. These satisfactory FIT performance results in the average-risk population suggest it could be an alternative to colonoscopy in the familial risk population, especially if the latter manages to significantly increase adherence to screening.

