#### Probabilistic sensitivity analysis.

Model robustness will be verified with a probabilistic sensitivity analysis using Monte Carlo simulation. For this purpose, the probability distribution functions representing the transition probabilities between states of the Markov model will be specified. Subsequently, results of model cost and effectiveness will be recalculated 10,000 times, taking random values of these distributions every time. Decision analysis, sensitivity analysis and Monte Carlo simulation will be performed with TreeAge (TreeAge Software Inc., Williamstown, Mass, USA).

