### Year 2 (February 2017 to February 2018)

- Completion of the 2^nd^ screening round in the FIT group
- Performance of colonoscopies of randomized patients (1^st^ to 4^th^ quarter), colonoscopies of patients with positive FIT results, repetition of incomplete colonoscopies and repetition of colonoscopies in which high-risk polyps were found or where piecemeal resection of these polyps was performed.

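### The cost-effectiveness model treats every colonoscopy as complete, so it leaves out the cost of repeat and substitute examinations, more of it in the colonoscopy arm

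*Supplement*

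**What the plan says.** The Cost-Effectiveness Analysis section of the Supplement sets seven criteria for a Markov model of 5000 relatives. Criterion 7 is "It will be assumed that all lesions detected at colonoscopy are resected and colonoscopies are carried out in full". Criteria 2 and 3 list the states. Neither contains an incomplete or repeated examination. The only repeat specified in the colonoscopy arm is a second-year colonoscopy after advanced neoplasia above 20 mm. Criterion 6 lists the cost items. Colonoscopy is one of them, but CT colonography, capsule colonoscopy and barium enema are not.

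The trial procedures differ from this. The Colonoscopy paragraph of Study variables and procedures requires adequate cleansing and caecal intubation, and continues: "Otherwise the colonoscopy will be considered incomplete and shall be repeated". The workplan for Year 2, and again for Year 3, includes "repetition of incomplete colonoscopies and repetition of colonoscopies in which high-risk polyps were found". The Study groups section offers the three substitute examinations to Group 2 when a full colonoscopy cannot be done.

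On robustness, the section promises a cost analysis "including sensitivity analysis of all variables in the model to test its robustness" and then names the variables: "adherence to the program, adherence to the various rounds of FIT screening, rate of complications, sensitivity and specificity of FIT and discount rate". In the probabilistic analysis, "the probability distribution functions representing the transition probabilities between states of the Markov model will be specified".

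**The concern.** Cost-effectiveness is secondary outcome b. The model's premise that examinations are always complete conflicts with procedures that the protocol itself writes down and schedules. Each repeat or substitute examination uses resources, and the model counts none of them.

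The omission is not neutral between strategies. Everyone screened in the colonoscopy arm has a colonoscopy, whereas in the FIT arm only those with a positive test do. Leaving out a fixed fraction of extra examinations therefore removes more cost from the colonoscopy arm, and substitute imaging is offered in the text only to that group. The numerator of the ICER, the cost of FIT minus the cost of colonoscopy, is shifted in favour of colonoscopy. The planned robustness checks are unlikely to show this, because completion is a fixed assumption with no probability attached to it.

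**Working it through.** The plan states no cost, yield or ICER figure, so there is nothing to reproduce. The calculation below only illustrates direction and order of size.

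**Inputs from the documents**
- Model cohort: 5000 (Cost-Effectiveness Analysis).
- Planned uptake: 50% colonoscopy, 60% FIT (Sample size calculation).
- Interim uptake: 34.1% colonoscopy, 35.9% FIT (Amendment 1).
- FIT specificity: 87% and 96% (Background).

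**Assumptions**
- Incomplete rate q = 5% to 15%, equal in both arms. The documents give no rate.
- Each incomplete examination leads to one further examination.
- Cumulative FIT positivity over three rounds = 1 − specificity³. This gives 1 − 0.96³ = 11.5% and 1 − 0.87³ = 34.1%. It treats rounds as independent, assumes all participants complete all three, and counts false positives only. True positives would raise it, and missed rounds would lower it.

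**Formulas**
- Colonoscopy arm examinations = 5000 × uptake.
- FIT arm examinations = 5000 × uptake × positivity.
- Omitted examinations = q × examinations.
- Net omission = q × (colonoscopy arm − FIT arm).

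| | Planned uptake | Interim uptake |
|---|---|---|
| Colonoscopy arm examinations | 5000 × 0.50 = 2500 | 5000 × 0.341 = 1705 |
| FIT participants | 5000 × 0.60 = 3000 | 5000 × 0.359 = 1795 |
| FIT arm colonoscopies | 346 to 1024 | 207 to 613 |
| Omitted, colonoscopy arm | 125 to 375 | 85 to 256 |
| Omitted, FIT arm | 17 to 154 | 10 to 92 |
| Smallest net omission | 0.05 × (2500 − 1024) = 74 | 0.05 × (1705 − 613) = 55 |
| Largest net omission | 0.15 × (2500 − 346) = 323 | 0.15 × (1705 − 207) = 225 |

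**Is the direction secure?** With equal q, the FIT arm would carry more of the omission only if cumulative positivity exceeded 2500/3000 = 83% at planned uptake, or 1705/1795 = 95% at interim uptake. With unequal q at planned uptake, the incomplete rate among FIT work-up examinations would have to be at least 2500/1024 = 2.4 times that in the colonoscopy arm.

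**Detection.** Suppose, only as a test, that the model took true prevalence as input and colonoscopy as perfect. The Background says that "between 20-26% of adenomas of any size and up to 6-12% of advanced lesions may be missed". Take an assumed prevalence of 10%, planned uptake, and the 29% and 80% FIT sensitivities quoted there.
- Colonoscopy arm: 5000 × 0.50 × 0.10 = 250 detections, falling to 235 (6% missed) or 220 (12% missed).
- FIT arm at 80%: 5000 × 0.60 × 0.10 × 0.80 = 240, falling to 226 or 211.
- FIT arm at 29%: 87, falling to 82 or 77.
- The FIT-to-colonoscopy ratio stays at 0.96 or 0.348, because work-up colonoscopies miss lesions too.
- The difference, which is the ICER denominator, shrinks by the miss rate. At 29% sensitivity, 163 becomes 153 or 143.

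**The case against.** The best defence is that criterion 7 is an openly stated simplification applied to both arms, in a secondary analysis, and that the plan promises sensitivity analysis of all model variables. It is also fair that a repeat colonoscopy can be priced with the existing colonoscopy item: what is missing there is the count, and only substitute imaging has no item at all. These points limit the weight of the concern but do not remove it. An equal assumption in both arms still omits unequal cost, and a completion rate fixed at 100%, with no state of its own, is not clearly one of the variables to be varied.

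A reader might go further and infer that the colonoscopy arm's yield is also too favourable, because the Background quotes a 6-12% miss rate. The documents do not support that, for three reasons:
- Criterion 7 covers completeness and the resection of lesions that were detected. It does not claim that all lesions are detected, so the miss rate does not contradict it.
- The plan says "Transition probabilities between the different states the subjects may undergo will be derived from the literature and results arising from this study". Detection rates observed in the trial already exclude missed lesions, and a further reduction would count them twice.
- Any miss also affects work-up colonoscopies in the FIT arm. Incomplete examinations are repeated or substituted, so incompleteness is not shown to lower yield.

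Nor can it be said that the reference test is never varied. The probabilistic analysis samples the transition probabilities, and the states include diagnosis of advanced neoplasia. Only completion falls outside it.

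**Conclusion.** The point holds for completeness and cost. The model's assumption conflicts with the protocol's own provision for incomplete, repeated and substitute examinations, and costs are understated in both arms, more in the colonoscopy arm. That direction rests on incomplete rates being broadly similar in the two arms and holds over the whole positivity range examined.

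The size is unknown. The net figures of 74 to 323 examinations per 5000 at planned uptake, and 55 to 225 at interim uptake, depend on an assumed incomplete rate and a rough positivity range. Without unit costs no change in the ICER can be given. No bias in the colonoscopy arm's yield is established. Nothing here affects the primary outcome of screening uptake.

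**What to change.** 1. Replace the completeness half of criterion 7 with the observed proportion of incomplete colonoscopies in each arm. The list of study variables does not name completeness or repeats, so whether they were recorded must be checked. If they were not, use a literature value and state its source.
2. Count repeat colonoscopies in both arms at the colonoscopy cost already in criterion 6.
3. Add a cost item to criterion 6 for substitute imaging, applied where the protocol offers it.
4. Add the completion or repeat rate to the named one-way sensitivity variables and to the probabilistic analysis.
5. State whether each detection input is an observed detection rate or a true prevalence from the literature. Only for a true prevalence, apply colonoscopy sensitivity equally in both arms and vary it.

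The cost is a few more inputs and a slightly more complex model.
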